#### Sample size

Sample sizes are calculated based on the primary outcome measure (SIPA) and our goal of ascertaining superiority of APT. The target sample size for this study is 80 participants, divided equally between the APT intervention and waitlist control group (40 participants per arm). This sample size provides 80% power to detect a medium-to-large effect size (d = 0.4) at a significance level of α = 0.05, while accounting for an anticipated attrition rate of 32.5%, as informed by the pilot study findings [14]. This sample size ensures that the study is adequately powered to evaluate the primary outcome of parental stress reduction. This sample size is achievable and able to capture the difference between arms.

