## Methods: assignment of interventions

### Randomisation

#### Sequence generation

Eligible participants who provide written informed consent will be randomly assigned to one of two groups: the APT intervention group or the waitlist control group. The randomisation unit is the family of the consulting parent. The randomisation process will employ a 1:1 allocation ratio. Restricted stratified block randomisation is used with three blocking variables: consulting parent’s age, gender and education. These variables were significantly related to the intervention’s outcome in the previous pilot study.

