#### Allocation concealment mechanism

Following baseline data collection, the RA will contact the collaborating statistician to randomly allocate the participant to APT or WL. RAs will be blind to group allocation.

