### Statistical methods

The primary analysis will compare the effectiveness of APT to the waitlist control condition, focusing on the SIPA scores at post-intervention. The primary outcome variable will be analysed using between-groups mean differences, and effect sizes will be calculated for the end-of-treatment and three- and six-month follow-ups. Outcomes will be predicted by mixed-effects linear regressions with special interest in allocation group and baseline group differences (if any). Secondary outcome variables will be analysed using mixed-effects models (linear and nonlinear, logistic or Poisson as appropriate). Partner attendance, adolescent attendance, working alliance and reflective function will be assessed in their role as predictors and/or mediators of change. The unit of analysis will be the referred parent, even when they have attended APT with their partner. Maintenance of effects will be examined by comparing outcomes at the six-month follow-up to post-intervention scores. An intention-to-treat approach will be employed for all analyses, ensuring that participants are analysed in the groups to which they were originally assigned, regardless of adherence to the intervention protocol.

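### The primary SIPA analysis is not tied to one method and baseline is mentioned only conditionally; always adjusting for baseline SIPA and the stratification factors would gain precision from data already collected

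*Protocol article*

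**What the plan says.** The Statistical methods section sets the primary comparison as APT against waitlist, "focusing on the SIPA scores at post-intervention". It then gives two consecutive statements of method. The first is "The primary outcome variable will be analysed using between-groups mean differences", with effect sizes to be calculated at end of treatment and at both follow-ups. The second is "Outcomes will be predicted by mixed-effects linear regressions with special interest in allocation group and baseline group differences (if any", closing the bracket there. Secondary outcomes get a separate sentence assigning them mixed models.

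Two other sections bear on the choice of model terms. Sequence generation states: "Restricted stratified block randomisation is used with three blocking variables: consulting parent’s age, gender and education", and justifies this with "These variables were significantly related to the intervention’s outcome in the previous pilot study". Allocation concealment mechanism states: "Following baseline data collection, the RA will contact the collaborating statistician to randomly allocate the participant to APT or WL". Baseline SIPA should therefore be available for every randomised parent, measured before allocation.

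**The concern.** Two points follow from the wording itself.

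- **Which analysis is confirmatory.** A simple difference in means and a regression estimate can give different estimates and p-values. The text does not rank them or say that one is obtained from the other. The separate mixed-model sentence for secondary outcomes makes it possible to read the mean difference as a stand-alone primary method. That leaves room to choose after the data are seen.
- **What baseline is for.** In a randomised trial, a baseline difference between arms is chance. A covariate earns its place by predicting the outcome, not by happening to differ between arms. Tying the interest in baseline to differences that may or may not appear invites the wrong criterion.

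The stratification factors are a supporting point. The article says they predict outcome and balances the arms on them, but the analysis text does not mention them. An analysis that ignores prognostic factors used to balance the arms overstates its standard error.

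The stake is precision. The trial expects to lose about a third of its parents and has little information to spare.

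**Working it through.** **Inputs from the protocol article**

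- Sample size section: "The target sample size for this study is 80 participants, divided equally between the APT intervention and waitlist control group (40 participants per arm"; d = 0.4; 80% power; alpha 0.05 (two-sided assumed, as the article does not say); attrition 32.5%.
- Evaluable per arm: 40 × (1 − 0.325) = 27.

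**Inputs assumed**

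- Correlation ρ between baseline and post-intervention SIPA: not given. The main range is 0.5 to 0.7, with 0.3 and 0.8 shown for reference.
- Share of outcome variance explained by the stratification factors, and number of strata: not given.

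**1. The plan's own figure.** The two-group formula without covariates is n per arm = 2(1.960 + 0.842)² / 0.4² ≈ 98.1, or 99 after rounding up. Inflating for attrition, 99 / 0.675 = 146.7, so 147 per arm and 294 in total. The stated 80 parents and 80% power are not reproduced. This is a separate problem; it matters here only because it sets the starting power.

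**2. Power without adjustment.** In SD units, SE = √(2/27) = 0.272. Power = Φ(0.4/0.272 − 1.960) = Φ(1.470 − 1.960) = Φ(−0.490) ≈ 31%.

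**3. Power with baseline always in the model.** The SE is multiplied by √(1 − ρ²).

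| ρ (assumed) | √(1 − ρ²) | SE reduction | SE | Power at d = 0.4, 27 per arm |
|---|---|---|---|---|
| 0 | 1.000 | 0% | 0.272 | 31% |
| 0.3 | 0.954 | 5% | 0.260 | 34% |
| 0.5 | 0.866 | 13% | 0.236 | 40% |
| 0.7 | 0.714 | 29% | 0.194 | 54% |
| 0.8 | 0.600 | 40% | 0.163 | 69% |

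For example, at ρ = 0.7: Φ(0.4/0.194 − 1.960) = Φ(0.098) ≈ 54%. Reaching 80% would need ρ of about 0.85 with 27 per arm, or about 0.77 if all 40 per arm were evaluable.

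**4. What conditional adjustment would do.** The article states no rule, so one was assumed for illustration: adjust only if a baseline t-test gives p < 0.05. Simulation used 27 per arm and 20,000 runs.

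| ρ | Type I error, conditional | Type I error, always adjusted | Power at d = 0.4, conditional | Power at d = 0.4, always adjusted |
|---|---|---|---|---|
| 0.5 | 4.3% | 4.8% | 30% | 38% |
| 0.7 | 3.6% | 4.9% | 30% | 51% |

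The rule triggers in about 5% of trials, so it almost always leaves baseline out. The always-adjusted powers are slightly below those in step 3 because the simulation uses the t distribution and allows for chance imbalance. Type I error falls below nominal under the conditional rule; it does not rise.

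**5. Stratification factors (direction only).** Suppose 80 parents are randomised in eight balanced strata and 54 remain after random dropout (20,000 runs). If the strata explain 10%, 20% or 30% of outcome variance, ignoring them gives a type I error of 4.3%, 3.6% or 2.8% for a nominal 5% test. This again is conservative. The eight strata and the variance shares are assumptions, so these figures show direction rather than a size for this trial.

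**The case against.** The strongest reply is that the two sentences describe one analysis: the mean difference is the quantity of interest and the mixed model estimates it. Such a model, with baseline as a covariate or as a repeated outcome, would already use the baseline correlation. The bracketed words may mean only that baseline differences will be looked at. A covariate list is normally left to the statistical analysis plan, which is not shown. Every size given above rests on a correlation that the article does not report.

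Much of this stands, and it rules out four stronger readings that a reader might infer:

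- *The plan specifies an unadjusted analysis.* The text never says so, and the next sentence names a regression model.
- *The plan excludes the stratification factors.* It is silent on them. Silence in a condensed article is not exclusion.
- *The plan breaches its own intention-to-treat commitment by using complete cases.* The article defines intention-to-treat as analysis by assigned group whatever the adherence. Nothing in the analysis text contradicts that, and a mixed model can use all available data.
- *Data-dependent adjustment inflates false positives.* The simulation shows the opposite for the rule tried.

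The reply does not show that the text fixes one primary method or commits to baseline adjustment. The one-analysis reading is plausible, but the reader has to supply it. What the article does say about baseline is conditional.

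**Conclusion.** The point holds as a defect of specification with a precision cost. Two methods are named for one primary outcome without a ranking, and baseline is worded so that its use can be read as depending on chance imbalance. Factors described as prognostic are not carried forward.

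The size depends on the conditional or unadjusted reading, on 27 evaluable per arm with equal attrition, and on an assumed ρ of 0.5 to 0.7. On those terms, the plan forgoes a 13% to 29% reduction in standard error, and about 9 to 23 percentage points of power at d = 0.4 (31% against 40% to 54%). If the intended mixed model already uses baseline SIPA, that loss disappears and only the unclear wording remains. Adjustment alone does not rescue the stated 80% power unless ρ is about 0.85.

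**What to change.** Rewrite the primary-analysis sentences in Statistical methods so that they:

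1. Name one confirmatory analysis: a linear mixed model for SIPA, with the APT-versus-waitlist contrast at post-intervention (T2) as the primary estimate.
2. Always include baseline SIPA and the three stratification factors (parent age, gender and education), whatever balance is observed. Enter the factors as a few main effects rather than as a full set of strata, given the sample size.
3. Delete the conditional words in brackets after the reference to baseline differences.
4. Report the raw difference in means as descriptive only.

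The cost is one paragraph, a matching entry in the statistical analysis plan, and a few degrees of freedom. No new data are needed. The Recruitment section expects recruitment to finish in Summer 2026 and no interim analysis is planned, so the change should be made and dated before outcome data are analysed. If a full protocol or analysis plan already specifies such a model, the article's wording need only be brought into line with it.

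### The primary SIPA estimate is described both as a raw post-intervention mean difference and as a mixed model; with 32.5% attrition expected, the plan should name one estimator, and it should use baseline

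*Protocol article*

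**What the plan says.** All references are to the protocol article.

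- **Time point and estimator.** Statistical methods describes the primary analysis as "focusing on the SIPA scores at post-intervention" and continues: "The primary outcome variable will be analysed using between-groups mean differences".
- **A second description.** The next sentence reads: "Outcomes will be predicted by mixed-effects linear regressions with special interest in allocation group and baseline group differences (if any". The sentence after that gives mixed-effects models to the secondary outcomes separately, so the second description can be read as covering the primary outcome too. Nothing says which of the two is decisive.
- **Intention-to-treat.** The section states: "An intention-to-treat approach will be employed for all analyses, ensuring that participants are analysed in the groups to which they were originally assigned", whatever their adherence.
- **Attrition.** Sample size sets 40 parents per arm, "while accounting for an anticipated attrition rate of 32.5%, as informed by the pilot study findings". The rate is not split by arm. It is not tied to T2, and it is not said to mean loss of outcome data as opposed to leaving therapy.
- **When T2 falls.** Data collection methods places T2 after six sessions in the APT arm and six weeks after T1 in the waitlist arm. Intervention and comparator sends the end-of-treatment battery to everyone in both arms, and Data collection methods has weekly reminders to parents until questionnaires come back.

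**The concern.** A difference in T2 means can be computed only from parents who return a T2 SIPA. Keeping those parents in their assigned groups is necessary for intention-to-treat, but it does nothing about who is absent. If the parents lost from one arm differ systematically from those lost from the other, the raw difference no longer estimates the effect in everyone randomised.

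There are two reasons to take this seriously here. The attrition rate comes from a pilot that, by the article's own account, had no control group, so it describes parents who were offered treatment and says nothing about parents waiting for it. And in the APT arm alone, T2 is defined by the number of sessions attended, which leaves the primary time point unclear for a parent who stops early.

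The choice between the two described estimators therefore matters. One ignores baseline SIPA. The other can use it and so remove the part of the selection that baseline explains. As the text stands, either could be reported as the primary result.

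**Working it through.** **The plan's own figures.** Expected numbers after attrition are 40 × (1 − 0.325) = 27 per arm, or 54 of 80, if all the attrition is missing T2 data. The stated power does not reproduce. A two-sided comparison of means at d = 0.4 and α = 0.05 needs 99 per arm before attrition, and 27 per arm gives about 31% power. That is a separate matter. The bias figures below do not depend on sample size.

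**Inputs.** From the article: 32.5% loss and d = 0.4, used here as the true effect in SD units. Assumed, because the article does not give them:
- all the loss is missing T2;
- baseline and T2 SIPA correlate ρ = 0.6;
- waitlist loss is random;
- APT loss follows a normally distributed drop-out score that correlates r with baseline stress, the top 32.5% being lost.

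**Scenario A: loss depends on baseline.** The cut-off on the drop-out score is c = Φ⁻¹(0.675) = 0.454, with density φ(c) = 0.360. Mean baseline among retained APT parents falls by r × φ(c)/0.675 = 0.533r SD. Their mean T2 score falls by ρ × 0.533r even without treatment. The raw difference relative to the truth is (0.4 + ρ × 0.533r)/0.4.

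| r | Shift at T2 (SD) | Raw difference ÷ truth | Using baseline ÷ truth |
|---|---|---|---|
| 0.3 | 0.6 × 0.160 = 0.096 | 0.496/0.4 = 1.24 | 1.00 |
| 0.5 | 0.6 × 0.267 = 0.160 | 0.560/0.4 = 1.40 | 1.00 |

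A large simulation gave the same ratios, with the last column from a regression of observed T2 on arm and baseline. With only T1 and T2, complete baselines, a common baseline mean and a common covariance, the likelihood-based longitudinal model gives the same arm difference as that regression. So what it buys is correction for loss that baseline explains. It does not recover the missing T2 scores.

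The sign follows the selection. With r = −0.3 or −0.5 (less stressed APT parents lost), the raw ratio is (0.4 − 0.096)/0.4 = 0.76 or (0.4 − 0.160)/0.4 = 0.60. If the same selection acts in both arms, the shifts cancel.

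**Scenario B: lost APT parents benefit differently.** Let lost parents gain a fraction f of what retained parents gain. The contrast in retained parents divided by the effect in all randomised is 1/(0.675 + 0.325f).

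| f | −0.25 | 0 | 0.25 | 0.5 | 0.75 | 1 | 1.25 |
|---|---|---|---|---|---|---|---|
| Ratio | 1.68 | 1.48 | 1.32 | 1.19 | 1.09 | 1.00 | 0.92 |

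At f = 0 the simulated baseline-adjusted estimate was also 1.48 times the truth. Modelling baseline does not help here, because the loss is tied to the unobserved benefit.

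**The case against.** The strongest reply is that the mixed-effects sentence already answers the point: the mean difference is the effect measure and the mixed model is how it will be estimated. That reading is fair, and it rules out the stronger inference that the trial will report a completer analysis under an intention-to-treat label. Nothing in the article restricts the analysis to completers or excludes parents without T2, and a mean difference by assigned group does not breach intention-to-treat as the article defines it. What survives is the ambiguity. The sentence that names the primary outcome gives it a mean difference, and the mixed-model sentence fixes neither the responses nor the role of baseline beyond a conditional interest in baseline differences.

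Three further objections stand in part:

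- The 32.5% may be loss from therapy more than loss of questionnaires. Sending the battery to everyone and weekly reminders both work against loss, so 54 of 80 is conditional. The article nevertheless builds the rate into its sample size.
- Bias in favour of APT is not established. Waitlist parents may also withdraw, and selective loss there could move the contrast either way.
- A reader might take 1.48 as a ceiling, or conclude that the trial has no safeguard against selective loss. Neither follows. The ratio runs from 1.68 to 0.92 over the values of f tried, and missing-data sensitivity analyses are commonly left to an analysis plan, which is not shown. Their absence from the article is not an error.

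**Conclusion.** The point holds in a limited form. The article describes two estimators for the primary outcome and does not say which decides the trial. One of them, the raw T2 mean difference, is open to selective loss that the intention-to-treat statement does not address. Under the assumptions listed, loss in the APT arm related to baseline stress makes the raw difference about 1.24 to 1.40 times the truth, and using baseline removes this. Where lost APT parents gain nothing, either estimator is about 1.48 times the truth, so naming the mixed model is an improvement and not a complete cure. These sizes are illustrations: the article gives neither the split of attrition by arm nor the correlations. Because the correction is cheap and settles what the trial's main result will be, it should be made.

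**What to change.** In Statistical methods, name a single primary estimator: a likelihood-based mixed model with T1 and T2 SIPA of all randomised parents as responses, a baseline mean common to both arms, and the arm difference at T2 as the treatment effect. Label any raw mean difference as descriptive for parents with observed T2 data. State that attrition will be reported by arm.

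A reference-based or delta-adjusted sensitivity analysis may be added to address loss related to unobserved benefit. It would be supportive, and not a condition for calling the result positive.

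The cost is a few sentences, slight extra programming and no new data. The downside is that the estimate may be less favourable than the raw difference.

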## Methods: monitoring

### Data monitoring committee

A data monitoring committee is not planned due to the low-risk nature of this intervention. No interim analyses are planned for this trial. Decisions to modify the trial will be made by the lead researcher, trial coordinator, trial sponsor, and REC.

### Trial monitoring

The study will be monitored by the CI (chief investigator), [name], and safety and efficacy will be reviewed by the CI and study co-applicants on a monthly basis. The research team will meet monthly in order to review study progress, and address any barriers or problems. Additional study oversight will be done by UCL Research Department of Clinical, Educational and Health Psychology. Ongoing data monitoring will be provided by an independent statistician. All research team members have completed training in data confidentiality either at Open Door, or another academic institution as part of the terms of their employment.

### Ethics 

#### Research ethics approval

Ethical approval for the RCT has been granted by the NHS ethics board Research Ethics Committee (REC) reference: 18/SC/0613, IRAS project ID: 254697.

#### Protocol amendments

Substantial protocol amendments will be submitted for approval to the REC and trial sponsor prior to implementation. Approved changes will be updated on the trial registry where applicable.

#### Consent or assent

The research team is aware that the study concerns vulnerable individuals, and potential risks and burdens have been carefully considered. The RA will obtain consent from participants. The RAs have received standardised training on study protocols and ethical considerations. Once the service user agrees to participate in the study, a phone call will be arranged with a RA to explain the study, obtain preliminary consent to be randomised, and complete preliminary consent procedures. A RA will then arrange an appointment to provide more information to the parent and sign informed consent forms. Participants will have the opportunity to ask questions and will be asked for consent for sessions to be filmed, which is optional. Adolescents who agree to participate will sign a consent/assent form. Adolescents will be informed that consent or assent can be withdrawn at any time, with no negative consequences to the adolescents or their parents. Proxy consent is not applicable for this study as all potential participants have decisional capacity to participate.

#### Confidentiality

Information collected in this study is sensitive, including records relating to participants' mental health and wellbeing and video-taped therapy sessions. Service users have no obligation to take part if they do not want their data to be used. Data collected during the study will be anonymised and will contain only a unique participant number as identification. A securely stored, encrypted file will contain the personal data associated to each participant, accessible only by the research team. Any paper-based information will be kept in locked storage at Open Door and will only be accessible by the research team and will be destroyed 6 months after the study has ended. No identifiable data will be transmitted to sponsors, co-investigators, and external parties.

#### Ancillary and post-trial care

If participants require further intervention following the completion of the study, they may have a discussion with their therapist, who can arrange continued provision of other intervention services in Open Door or refer them to other service providers if necessary.

## Discussion

This study aims to provide robust evidence on the effectiveness of a brief, individualised parenting intervention—APT—for parents of adolescents experiencing clinically significant levels of stress. By including a control group and a follow-up period, the trial addresses key limitations of the earlier pilot study [14]. If demonstrated to be effective, APT could serve as an accessible and engaging intervention, supporting parents and ultimately contributing to improved outcomes for adolescents and their families.

The key strength of this study lies in its pragmatic trial design, conducted in a real-world clinical setting, which enhances the ecological validity of the findings. The inclusion of both parent- and adolescent-reported outcomes adds depth and breadth to the evaluation, capturing multiple perspectives on the impact of the intervention.

However, this study has some limitations. The use of waitlist controls, while addressing ethical considerations, does not account for non-specific treatment effects, which could impact the interpretation of the findings. Future research could build on this design by comparing APT with an active control condition, enabling a more precise understanding of the specific mechanisms of action of the intervention.

Overall, this trial represents a significant step forward in the evidence base for parenting interventions targeting parents of adolescents. Given the well-established influence of parenting on adolescent outcomes, effective and accessible interventions in this domain have the potential for substantial public health benefits. Findings from this study will not only inform clinical practice but also contribute to policy decisions and broader implementation strategies, amplifying its impact on adolescent mental health and wellbeing.

